## Abstract

**Background:**

The prevalence of depression in people with a visual disability is high but screening for depression and referral for treatment is not yet an integral part of visual rehabilitation service provision. One reason for this may be that there is no good evidence about the effectiveness of treatments in this patient group. This study is the first to evaluate the effect of depression treatments on people with a visual impairment and co morbid depression.

**Methods /design:**

The study is an exploratory, multicentre, individually randomised waiting list controlled trial. Participants will be randomised to receive Problem Solving Therapy (PST), a ‘referral to the GP’ requesting treatment according to the NICE’s ‘stepped care’ recommendations or the waiting list arm of the trial. The primary outcome measure is change (from randomisation) in depressive symptoms as measured by the Beck’s Depression Inventory (BDI-II) at 6 months. Secondary outcomes include change in depressive symptoms at 3 months, change in visual function as measured with the near vision subscale of the VFQ-48 and 7 item NEI-VFQ at 3 and 6 months, change in generic health related quality of life (EQ5D), the costs associated with PST, estimates of incremental cost effectiveness, and recruitment rate estimation.

**Discussion:**

Depression is prevalent in people with disabling visual impairment. This exploratory study will establish depression screening and referral for treatment in visual rehabilitation clinics in the UK. It will be the first to explore the efficacy of PST and the effectiveness of NICE’s ‘stepped care’ approach to the treatment of depression in people with a visual impairment.

**Trial registration:**

ISRCTN46824140

## Background

The presence of a visual impairment is known to increase the risk of depression and it is an independent predictor of suicide in the elderly [1,2]. Epidemiological studies indicate that the prevalence of depression in visually impaired older adults living in the UK is 13.5% compared to just 7.4% for those without a visual impairment [3]. At the time visually impaired people most need help, when they are accessing vision rehabilitation services, data from North America indicates that the prevalence of depression is higher still at about 30% [4]‐[7].

Low vision rehabilitation services operate at the interface between health and social care and, in the UK, typically involve optometrists working with social services and the voluntary sector. The aim of this intervention is to promote independent [8] living by reducing the disability associated with visual impairment. More specifically, people with low vision are provided with practical solutions to specific problems e.g. by providing magnifiers to help with reading, improved lighting and modifications to the home [9]. However, although these services have been shown to reduce disability and people appreciate the low vision aids provided, their reported effects on overall quality-of-life have been modest [10]‐[12]. One contributory factor is likely to be untreated depression in this patient group. Depression is not only disabling in its own right but is very likely to act as a barrier to good vision rehabilitation outcomes [13,14].

Despite the fact that people with a visual impairment have an increased risk of depression, depression screening and referral for treatment is not currently part of vision rehabilitation service provision. One reason for this apparent omission may be that there is no good evidence about the effectiveness of depression treatments in this specific patient group. For example, although the National Institute for Health and Clinical Excellence (NICE) have issued guidance on the management and treatment of depression in people with chronic health problems there is no evidence about the effectiveness of the recommended ‘stepped care’ approach in people with a visual impairment [15]. The ‘stepped care’ treatment options include: physical activity programmes, group-based peer support (self-help) programmes, individual guided self-help programmes based on the principles of CBT including behavioural activation and Problem Solving Therapy (PST) and, antidepressants. Although there is no direct evidence about the effectiveness of these interventions in people with depression and a visual impairment, the ability of PST to prevent the onset of depression in people with age-related macular degeneration, the leading cause of visual impairment in the developed world, has been studied [8]. In that study PST was shown to be successful at 2 months but the effects were less impressive at 6 months.

The Depression in Visual Impairment Trial (DEPVIT) will establish depression screening in several UK based vision rehabilitation centres and obtain preliminary data about the treatment effects associated with the stepped care approach recommended by NICE and PST. More specifically, DEPVIT aims to estimate the prevalence of depressive symptoms using the Geriatric Depression Scale (GDS-15) in an observational study of consecutive attendees of low vision services in England and Wales, and compare 2 interventions, PST and ‘referral to the GP’, against a waiting list control for newly-diagnosed low vision patients with depressive symptoms in an exploratory randomised controlled trial. Subsidiary aims include determining what action GPs take in response to a referral for depressive symptoms in this patient group, determining the acceptability of these interventions to patients and establishing economic information about the cost to roll-out a psychological problem solving based intervention for people experiencing sight loss and how well standard economic tools work with people experiencing sight loss.

## Methods/design

This is an exploratory, multicentre, individually randomised controlled trial. Figure 1 summarises the study design and the flow of patients through the trial.

**Figure 1 F1:**
[figure not shown]
DEPVIT Trial Design.

### The interventions

This trial involves 2 active interventions PST and ‘referral to the GP’ and a ‘waiting list control’.

The PST intervention evaluated in this study is a behavioural therapy that has been specifically designed for people with a visual impairment [8]. This intervention involves a trained psychological therapist working with the patient in their own home or at one of the research centres. Over a 6–8 week period, patients are taught a 7-step method for approaching and solving their problems. The steps are: (1) defining the problem; (2) establishing realistic goals; (3) brainstorming solutions; (4) implementing decision making guidelines (Pros versus Cons); (5) choosing a preferred solution; (6) implementing the solution; and (7) evaluating the outcome. The PST intervention will also include additional self-help materials for patients e.g. materials concerning an explanation of depression, a discussion on the importance of treating depression, and a description of the various treatment options as well as vision related sign posting materials. This type of behavioural therapy is an individualised guided self help approach consistent with NICE guidelines [15]. Optometrists providing the low vision assessment will share the patient’s ‘treatment plan’ with the therapist (via a brief report) so that the therapist can help the patient implement the optometrist’s recommendations via the PST framework if this is what the patient wishes. To ensure the fidelity of this intervention the PST therapists will be trained by [name] the Clinical Psychologist who originally designed the PST intervention used in 2007 by Rovner, Casten et al, [8]. With the participants consent, each PST intervention will be taped and one third of randomly selected tape recordings will be reviewed to ensure the fidelity of the intervention.

The second intervention is ‘referral to the GP’. A carefully crafted referral letter will inform the GP that their visually impaired patient has screened positive for a possible depressive disorder and invites them to offer the patient an assessment and treatment as per NICE guidelines for the management of depression. This is a pragmatic intervention and we acknowledge that GPs may or may not adhere to NICE guidelines i.e. we propose to evaluate the effectiveness of the referral, not ‘best practice’ as described by NICE. The fidelity of this intervention will be assessed by recording the number of correctly addressed referral letters sent.

The final arm of the study is a ‘waiting list control’. Patients in this arm of the trial will be referred to their GP using the referral letter described above after the 6 month outcome measure. A ‘waiting list control’ provides people taking part in the study with a better level of care than ‘treatment as usual’ because depressive symptoms are currently ignored and there is no referral. The fidelity of this intervention will be assessed by asking people at 6 months about any treatments received during the time of the study.

In addition to the interventions listed above, all participants in the study will have a follow up vision rehabilitation appointment 6 weeks after the initial appointment. Follow up appointments of this type are typical for people who appear depressed or are obviously struggling at the initial low vision assessment.

### Outcome measures

The primary outcome will be the change in depressive symptoms, from randomisation to 6 months, as measured by the Becks Depression Inventory (BDI-II). The BDI-II is a reliable, valid and widely used outcome measure for depression [16,17].

Secondary outcome measures in this exploratory trial will include change (from randomisation to 3 and 6 months) in visual disability as measured using the 7 item NEI VFQ and the near vision subscale of the VFQ-48 and, change in ‘generic health related quality of life’ as measured using the EQ-5D [18,19]. Additional secondary outcomes measured at 6 months will include the proportion of people still screening positive for depression as measured with the GDS-15, participant’s use of services as determined using a Client Services Receipt Inventory (CSRI) and an economic measure of ‘capability and wellbeing’ the ICECAP-O [20]‐[22]. At the end of this exploratory trial participants will be asked about any treatments for depression they have received during the trial period (specifically, whether they received regular review and support by their GP, referral to a community mental health team, supportive psychotherapy, counselling, problem-solving therapy, cognitive-behavioural therapy or antidepressant therapy). They will also be asked about the acceptability of any interventions received. Participants in the waiting list control group who still screen positive for depression (GDS-15, 6+) will be referred to their GP. And, 3 months later asked about any treatment for depression received as a result of the referral.

All trial outcomes will be assessed by telephone interview by the Study Coordinator who will be masked to the treatment intervention. In order to minimise ‘loss to follow up’, interviews will be based on a standard script and will remind participants of their valuable contribution and the need to complete the study.

### Sample size

During the course of the study 1000 consecutive attendees will be screened. At the outset we anticipate that about 1/3 will screen positive for depression and be eligible, and that of those, about 100 will consent to take part. This target of 100 patients recruited into the trial is realistic and achievable. Resource limitations require us to cap the number of participants to 150.

Since this study is exploratory we will predominantly use descriptive methods to report results. That is, this study is not powered to look at differences in outcomes (there is no data upon which to determine the sample size). However, to give the reader some indication about the power of this exploratory trial, if we assume that those entering the trial are moderately depressed (average BDI-II score of 30, SD 10.5) and, if the trial finishes with only 20 participants per treatment group, we would have 83% power to detect a difference in post treatment means of 10 (a change of 10 units corresponding to a moderately important clinical difference) with a 5% two-sided significance level.

### Recruitment

Participants will be identified and recruited from 7 community based low vision rehabilitation centres in South Wales and from one large secondary care based low vision rehabilitation centre at Guys and St Thomas’ NHS Trust, London [23]. Based on known activity in these recruitment centres we anticipate that the 7 sites in Wales will screen approximately 500 people in total and that a similar number will be screened in London.

### Inclusion criteria

Adults (18+ years of age) with a score of at least 6 on the GDS-15 (administered as part of the routine pre assessment questionnaire) will be the inclusion criterion for this study.

### Exclusion criteria

To ensure our results are applicable to the population we propose to keep the exclusion criteria to a minimum, specifically: 1) those who have already had a low vision assessment within the previous 12 months, 2) those who are referred to the clinic in error (i.e. so visually impaired that low vision care and follow up are inappropriate or, so visually able (e.g. following refraction) that there are no low vision needs), 3) those already being treated for depression including psychotherapeutic and psychopharmacological treatments, 4) inability to understand English, 5) Inability to use the telephone e.g. caused by very poor hearing, 6) severe medical illness that would preclude participation in a 6 month study, 7) a score of 2 or 3 on the BDI-II question about suicidal ideation, all people in this group will be urgently referred to their GP, 8) those screening positive for significant cognitive / memory problems as determined with a modified version of the MMSE will be excluded.

### Trial procedures: consent, baseline assessments and randomisation

The low vision rehabilitation services in Wales and London now include a routine self-complete pre assessment questionnaire (made up of the 7 item NEI VFQ and GDS-15) which is given to patients one week before their consultation. During the trial this will be accompanied by a Patient Information Sheet letting people know that the low vision service they are about to attend is taking part in a study. The sheet details the aims, purpose and what is involved in participation in the study. At the rehabilitation consultation, those satisfying the inclusion criteria will be invited to take part by the optometrist who provides the low vision rehabilitation intervention.

The optometrists (who are trained to take informed consent) will document the consultation using standard clinical records and, for the purposes of this study, a case report form. The GDS-15 will be reviewed at the start of the hour long low vision assessment and all positive screening patients will be informed that they may be eligible to take part in the study. Toward the end of the low vision assessment a full verbal explanation of the study will be provided to positive screening patients and they will be asked if they would like to take part. Those expressing an interest in taking part will then be screened by the optometrist for exclusion criteria 1, 2, 3, 4, 5 & 6. Those still eligible will be given written copies (large print) of the questionnaires that will be used in the telephone interview to take home and will be asked to provide their written informed consent.

Consenting patients will be contacted by the Study Coordinator within 1 week to, make an appointment to administer the cognitive screen and BDI-II to check for the exclusion criteria 7 and 8. Those meeting the additional eligibility criteria will be enrolled in the study and the other baseline outcome measures will be administered. Those scoring 29 or more on the BDI-II at the baseline interview have severe depressive symptoms and in all cases a letter will be written to the person’s GP requesting a ‘medication evaluation’.

Potential recruits who would like additional time to consider enrolment, after the initial low vision assessment will be contacted by phone by their low vision practitioner one week later to find out “how they are getting on”. If they then want to take part in the study they will be booked back in to see the practitioner to complete the study consent form. Participants who screen positive for depression but who decline to take part in the trial will be asked if they would like to be referred to their GP anyway. The person’s decision will be noted in the records e.g. if they decline referral. These people will be asked if they are willing to provide their consent for the use of anonymous baseline data.

Within one week of the baseline telephone interview, participants will be randomised using computer generated permuted blocks of varying sizes (unknown to investigators) stratified for study centre (Wales and London) and for ‘medication evaluation’ only. To ensure that the Study Coordinator is masked to treatment allocation, the Chief Investigator will allocate participants to the different arms of the trial.

For those assigned to the ‘referral to GP’ arm of the trial, the letter to the GP will be posted on the day the person was randomised and the participant will be asked to make an appointment with their GP within 2 weeks. For those assigned to PST, treatment will commence within 2 weeks of randomisation. All participants will be given a follow up vision rehabilitation appointment 6 weeks after the initial rehabilitation appointment.

The Study Coordinator will contact participants 3 and 6 months after randomisation to obtain outcome measure data.

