### Analyses

#### Statistical analyses

We will tabulate the number of patients by GDS-15 Score. We will estimate the prevalence of depressive symptoms (defined as a GDS-15 score of 6 or more) with 95% confidence intervals computed by the exact binomial method. We will use logistic regression to assess whether factors such as age, sex, pathology and site are associated with depressive symptoms. With a sample size of 1000, a two sided 95% confidence interval will extend 0.028 from the observed proportion for an expected proportion of 0.3.

This trial is the first of its kind and hence ‘exploratory’. For the trial, we will compare baseline characteristics of the allocated groups to ensure the adequacy of randomisation (including duration of visual loss). If outcome data are not available for all randomised patients, we will compare characteristics of those for whom it is available with those for whom it is not to assess whether the groups differ systematically. To retain the validity of the randomisation process the analyses will be undertaken on an intention-to-treat basis.

We will report average change in BDI scores in treatment groups using the mean or median as appropriate together with some indication of variability such as the standard deviation or interquartile range. These results will then be used to estimate the numbers of patients required for a definitive study.

Missing data has the potential to bias our findings. Hence we will attempt to minimise ‘loss to follow up’ by making it clear to potential recruits what is required at the outset, letting them know that completion of the study is important and reminding them of the value of their contribution when outcomes are assessed during the scripted telephone interviews. We will document the reasons for missing data and establish both the extent and patterns of missing data in each arm of the trial. We will also acknowledge the potential impact of missing data in our conclusions.

We will also compare the characteristics (age, sex, level of depression, level of vision impairment, ethnicity, functional ability and time since vision loss first identified) of those who did and did not consent to take part in the trial to determine if we can predict who is likely to benefit from depression screening.

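### Randomisation is stratified by centre and by baseline BDI-II severity, but the BDI-II change summaries used to size the definitive trial take no account of either stratum: a modest, conservative loss of precision

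*Protocol article*

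**What the plan says.** The section on trial procedures (consent, baseline assessments and randomisation) describes permuted blocks "stratified for study centre (Wales and London") and, as the only other factor, for medication evaluation. That makes four strata. The same section ties the second factor to the baseline score: "Those scoring 29 or more on the BDI-II at the baseline interview have severe depressive symptoms", and all of these participants have a letter sent to their GP asking for a medication evaluation.

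Under Outcome measures, "The primary outcome will be the change in depressive symptoms, from randomisation to 6 months", measured by the BDI-II. One stratification factor is therefore a two-way cut of the baseline value of the primary outcome.

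The Statistical analyses section says: "We will report average change in BDI scores in treatment groups using the mean or median as appropriate together with some indication of variability", giving the standard deviation or interquartile range as examples. It continues: "These results will then be used to estimate the numbers of patients required for a definitive study". Neither stratification factor appears in this summary. Centre enters the trial analysis only as a London-versus-Wales comparison of outcomes within the PST arm.

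The Sample size section says the trial is not powered for differences in outcome, and adds: "Since this study is exploratory we will predominantly use descriptive methods to report results".

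**The concern.** Stratified randomisation makes the arms nearly equal on the stratification factors. Variation between strata then contributes little to the real error of an arm difference, yet it remains in an SD pooled over the strata. If the factors predict the outcome, a standard error built from that SD is larger than it needs to be, and precision gained by the design is not used.

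Two things are at stake. Any arm difference in BDI-II change would be reported less precisely than the data allow, in a trial that may finish with 20 per arm. And the section names the next use of its results: sizing the definitive study. If that study is analysed with adjustment for these factors, the relevant SD is the residual SD, which the stated summaries do not provide.

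**Working it through.** **The plan's own figure.** The Sample size section gives 83% power for 20 per arm, a difference of 10, SD 10.5 and two-sided 5%. The standard error is 10.5 × √(2/20) = 3.32 and the noncentrality 10/3.32 = 3.01. With 38 degrees of freedom the two-sample t-test has 83.5% power, so the figure reproduces. It is a calculation without stratum terms.

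**Inputs**
- Baseline BDI-II: mean 30, SD 10.5 (Sample size). Normality is assumed.
- Cut at 29 or more (trial procedures), taken as 28.5 with continuity correction.
- Equal SDs at baseline and 6 months: assumed.
- Correlation ρ between baseline and 6-month BDI-II: not given, so 0.3 to 0.9 is assumed.

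**Step 1: information in the cut.** c = (28.5 − 30)/10.5 = −0.143, so the share at or above the cut is p = 0.557. The share of the baseline's linear information that the cut keeps is φ(c)²/[p(1 − p)] = 0.632.

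**Step 2: variance of change explained.** With equal SDs, the squared correlation of change with baseline is (1 − ρ)/2. The medication stratum therefore explains R² = 0.632 × (1 − ρ)/2.

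**Step 3: consequences.** The SD of change is 10.5 × √[2(1 − ρ)]. The residual SD is that value times √(1 − R²). The standard-error ratio is 1/√(1 − R²) and the sample-size ratio 1/(1 − R²).

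| ρ (assumed) | R² | Raw SD of change | Residual SD, stratum | SE excess | N excess | Residual SD, continuous baseline |
|---|---|---|---|---|---|---|
| 0.3 | 22% | 12.4 | 11.0 | 13% | 28% | 10.0 |
| 0.5 | 16% | 10.5 | 9.6 | 9% | 19% | 9.1 |
| 0.7 | 9.5% | 8.1 | 7.7 | 5% | 11% | 7.5 |
| 0.9 | 3% | 4.7 | 4.6 | 2% | 3% | 4.6 |

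Cutting at exactly 29 (p = 0.538) gives R² = 0.222 at ρ = 0.3, and 1/(1 − 0.222) = 1.29, hence an upper end of 29%. The last column is 10.5 × √(1 − ρ²).

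**Step 4: what the sample-size ratio means.** For an assumed difference of 5 points at 90% power, n per arm from the raw against the stratum-adjusted SD is 130 v 102, 93 v 79, 56 v 51 and 19 v 18 at ρ = 0.3, 0.5, 0.7 and 0.9.

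**Step 5: simulation.** With 40 patients in two arms and permuted blocks within four strata, the average unadjusted standard error against its true value was 3.92 v 3.49, 3.30 v 3.12, 2.56 v 2.41 and 1.48 v 1.46 for the same four correlations. When the strata did not predict change there was no excess (3.31 v 3.33).

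With three arms and 60 randomised and completing, unadjusted 95% intervals covered about 96% to 97% at ρ of 0.7 to 0.3. With 100 randomised and 60 random completers, coverage was about 96%, because dropout undoes part of the forced balance.

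**The case against.** The strongest reply is that the plan states no test, standard error, confidence interval or model for an arm comparison. It is mainly descriptive, and naming stratification factors as covariates is usually left to the analysis plan, which is not shown. This stands against any claim that the trial will publish wrong intervals. A reader might infer that from the unstratified SDs, but an SD describes spread and is not an error bar. What remains is that the section does state a summary and its use in sizing the next trial, and that use can be assessed.

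A reader might also infer that the SD itself is inflated. It is not: the arm SD correctly estimates the marginal SD. It is too large for planning only if the definitive trial adjusts for these factors or for baseline, and the article does not say whether it will.

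It is tempting to add a gain from centre. The Recruitment and Challenges sections show different settings and optometrist training, but Challenges also says the two services agreed a standardised approach, and no outcome difference is given. Any centre figure would be pure assumption.

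Nor is the gain separate from baseline adjustment. Under the normal model used here, the medication stratum adds nothing once continuous baseline BDI-II is in the model. The stratum-only residual SD would itself oversize a baseline-adjusted trial by about 20%, 12% and 6% at ρ = 0.3, 0.5 and 0.7, for example (11.0/10.0)² at 0.3 before rounding.

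Finally, the correction is smaller than the sampling error of a pilot SD. With 57 degrees of freedom (60 completers, three arms) its 95% limits are about −15% to +22%. That limits the importance of the point. It does not remove it, because the raw-SD excess is systematic and avoidable at no cost.

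**Conclusion.** The point holds in a limited form. Randomisation uses two stratification factors, one of them a cut of the baseline of the primary outcome. The stated summaries of change use neither, and they feed the definitive sample size.

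From the medication stratum alone, an arm difference based on the raw SD has a standard error about 2% to 13% larger than a stratum-adjusted one, for assumed correlations of 0.9 down to 0.3. A definitive trial analysed with adjustment but sized from the raw SD would be about 3% to 29% too large. These figures rest on normality, equal SDs and an unstated correlation. If the strata did not predict change, there would be no excess.

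The error is conservative: it costs precision, does not bias the estimated difference and produces no false claim of benefit. It is a worthwhile improvement to a stated method and does not threaten the trial's conclusions.

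**What to change.** In the Statistical analyses section:
- Keep the raw arm means (or medians) and SDs (or IQRs) of BDI-II change as descriptive results.
- State that any arm difference in BDI-II change will be estimated, with a 95% confidence interval, from a model with centre (Wales/London) and medication evaluation (yes/no) as factors. Using continuous baseline BDI-II would capture the medication-stratum gain and more.
- Report that model's residual SD beside the raw SD, and use it to size a definitive trial only if that trial will be analysed the same way.

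The cost is a sentence or two of wording and two degrees of freedom. Both factors are known for every randomised participant. No new data and no change to randomisation or follow-up are needed.
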